### Frequency and plans for auditing trial conduct {23}

Not applicable. No auditing is planned in this trial. The PIs will meet weekly during the study period to review trial progress.

### Plans for communicating important protocol amendments to relevant parties (e.g., trial participants, ethical committees) {25}

Before making any protocol modifications, approval must be obtained from the Ethics Committee of Shanghai Sixth People’s Hospital. If approved, these modifications must be reported in the trial register and included in the final report of research data.

### Dissemination plans {31a}

Clinical trial results are expected to be published in scientific medical journals and national and international conferences. The first and corresponding author will hold primary responsibility for the publication of the results of this clinical trial.

## Discussion

The pathological mechanism of viral pneumonia mainly involves a series of “cytokine storms,” tissue edema, vascular endothelial damage, increased vascular permeability, and thrombosis, which leads to a series of clinical symptoms, and may occur dyspnea or impaired oxygenation in severe cases [23, 24]. At present, the focus of treatment for diagnosed patients is symptomatic and we try to use the mechanical and biological effects of LIPUS for treatment.

On the one hand, specific ultrasound intensity, frequency, pulse width, and duration are used for non-invasive physical therapy, and on the other hand, the anti-inflammatory, anti-thrombotic, and pro-reparative effects of LIPUS are combined to relieve the lung condition and reduce the clinical symptoms of patients. Mitogen-activated protein kinase (MAPK) and nuclear factor-kappa B (NF-κB) are classical inflammatory response pathways. A large number of studies have found that the above inflammatory pathways are significantly inhibited after LIPUS irradiation and inflammatory cytokines such as TNF-α, IL-1β, and IL-6 decreased accordingly [25, 26]. The potential of LIPUS to regulate the phenotype of inflammatory cells and reduce the number of neutrophils and inflammatory macrophages was also observed in the musculoskeletal injury model [27, 28].

In this study, we randomly divided patients with viral pneumonia into three groups and evaluated the efficacy of LIPUS by comparing the pulmonary inflammatory state after treatment with the control group and the self-control group. In addition to the control group, we also set up a self-control group to better eliminate the impact of individual differences on the results. If the research results suggest that the curative effect of the LIPUS treatment group is significantly better than that of the control group and the self-control group, it indicates that the LIPUS treatment is effective; if the curative effect of the LIPUS group is better than that of the control group, but there is no difference with the self-control group, it indicates that the LIPUS intervention effect is fair. The statistical difference may be due to individual differences, and the sample size needs to be further expanded for evaluation; if the curative effect of the LIPUS group is not statistically different from that of the control group and the self-control group, LIPUS therapy can be considered poor.

To date, no adverse events have been reported during LIPUS treatment. However, the exact biological effects of LIPUS in tissues are not fully understood. Although LIPUS has been investigated in many therapeutic applications experimentally or clinically and achieved good curative effects [29–31], further research is still needed to fully understand the exact mechanism in humans.

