Participants in the self-control group will be compared the LIPUS-treated area with the non-treated area in the lungs. First, a CT examination is performed to locate the body surface of the inflammatory exudative area. If the patient has bilateral pulmonary exudative inflammation, LIPUS treatment will be performed on one side of the lung, and the other will serve as the self-control group. Limited by the frequency of LIPUS, ultrasound cannot penetrate through one lung tissue to the other, and its maximum penetration depth is limited to the inside of the target lung. If the patient has unilateral pulmonary exudative inflammation, the inflammatory area will be divided into the upper and lower areas, and a single-area stimulus will be performed. The diameter of the two ultrasound probes is approximately equal to the width of the intercostal space, and the probes can be placed in the same intercostal space or in different intercostal spaces. The direction of sound beam can be adjusted manually. Limited by the width of the sound beam and the plane of sonication, the non-target inflammatory area above or below can be considered not to be affected.

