## Outcomes {12}

### Primary outcome

The primary outcome measure will be the difference in the extent of absorption and dissipation of lung inflammation on CT images. Result comparisons will be made between the test group and the control group and between the LIPUS-treated and non-treated areas within the self-control group.

Pulmonary inflammation on CT images will be assessed by an expert chest radiologist before and 7 days after treatment to compare the area and volume of inflammation in the target area of the lung, as well as the area absorption rate (AAR) or volume absorption rate (VAR). A Pair software will be used to mark and 3D reconstruct the target area of CT images and record the data of pulmonary inflammation changes. AAR is defined as [(target site inflammation area before treatment − target site inflammation area after treatment)/target site inflammation area before treatment] × 100 (%). VAR is defined as [(target site inflammation volume before treatment − target site inflammation volume after treatment)/target site inflammation volume before treatment] × 100 (%).

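### The Discussion's rule for judging LIPUS does not match the primary comparisons and can mislabel the result, by an amount that depends on which self-control area is compared

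*Protocol article*

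**What the plan says.** The Discussion section of the protocol sets out three verdicts.

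- *Effective*: the LIPUS result is "significantly better than that of the control group and the self-control group, it indicates that the LIPUS treatment is effective".
- *Fair*: LIPUS is better than control, "but there is no difference with the self-control group, it indicates that the LIPUS intervention effect is fair". The text adds that the difference might then reflect individual differences and that a larger sample would be needed.
- *Poor*: the LIPUS result "is not statistically different from that of the control group and the self-control group, LIPUS therapy can be considered poor".

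The Intervention description {11a} shows that patients in the self-control arm are treated with LIPUS. In bilateral disease, "LIPUS treatment will be performed on one side of the lung, and the other will serve as the self-control group". In unilateral disease, "the inflammatory area will be divided into the upper and lower areas, and a single-area stimulus will be performed".

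The Primary outcome section makes its comparisons "between the test group and the control group and between the LIPUS-treated and non-treated areas within the self-control group". It plans no comparison of the LIPUS arm with the self-control arm. The absorption rates AAR and VAR are defined there at the target site.

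**The concern.** Three things are wrong with the rule as worded.

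1. **It uses a contrast that the primary outcome does not plan.** The best verdict needs the LIPUS group to beat the self-control group. The Primary outcome section uses that arm only for a within-patient contrast.
2. **The comparator is not defined.** Each self-control patient has a treated and an untreated area. If the treated area is compared, a treatment that works should show no difference from the LIPUS arm. Similar benefit there would support efficacy, yet the rule downgrades that pattern to *fair* and suggests individual differences as the cause. Randomization already guards the LIPUS versus control contrast against systematic differences between patients.
3. **The last limb reads non-significance as lack of efficacy**, in a trial of about 22 per arm whose size rests on no stated effect.

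At stake is the published conclusion. The same data could be called effective or fair depending on an unstated choice, and an inconclusive trial could be reported as showing poor efficacy.

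**Working it through.** **Inputs from the protocol.** Sample size {14}: 66 participants, 1:1:1, two-sided α = 0.05, power 90%, about 5% dropout, 70 in total. Statistical methods {20a}: independent-sample test between groups, paired-sample test within the group before and after treatment, significance level 0.05.

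**The plan's own figure.** 66/0.95 = 69.5, rounded up to 70, so the inflation reproduces. The 66 cannot be recomputed, because no effect size or SD is given. 66/3 = 22 per arm.

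**Assumed effect.** The standardized effect at which 22 per arm gives 90% power is (1.960 + 1.282) × √(2/22) = 0.977 by the normal approximation. I use 1.0 SD as the round value. With a t-test, the noncentrality is 1.0 × √(22/2) = 3.317 on 42 degrees of freedom, which gives 90.0% power for LIPUS versus control. I also use 0.5 SD. Both are assumptions.

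**The rule as worded.** I simulated three arms of 22 with unit SD, control mean 0, LIPUS mean d and self-control mean f × d, using two-sided t-tests at 0.05. Here f = 1 for the treated area, 0.5 for the average of both areas (unit SD kept) and 0 for the untreated area. LIPUS is assumed to have no effect on untreated areas.

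| Self-control value compared | *Effective*, d = 1.0 | *Fair*, d = 1.0 | *Poor*, d = 1.0 | *Poor*, d = 0.5 |
|---|---|---|---|---|
| Treated area | 2.5% | 86% | 9% | 60–61% |
| Average of both | 36% | 54% | 9% | 59–60% |
| Untreated area | 83% | 7% | 3% | 48% |

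On the treated-area reading the chance of *effective* stays near 2.5% even at d = 2.0, since the two arms then have the same mean.

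The 36% depends on the unit SD for the average. If each area has unit SD and the within-patient correlation is r, the average has SD √((1 + r)/2). The figure is then 40% at r = 0.5 and 46% at r = 0.

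With 20 per arm (the Abstract gives sixty participants) and d = 0.977, *effective* is reached in 2.5%, 31% and 76% on the three readings. With 22 per arm at the same d it is 2.4%, 34% and 81%.

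**A rule built on the planned comparisons.** Require LIPUS versus control and the paired treated-versus-untreated difference both to be significant. The paired noncentrality is d/√(2(1 − r)) × √22 on 21 degrees of freedom. The two tests use different patients, so their powers multiply. At d = 1.0:

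- r = 0: 0.885 × 0.900 = 80%
- r = 0.3: 0.965 × 0.900 = 87%
- r = 0.5: 0.994 × 0.900 = 89%
- r = 0.7: 1.000 × 0.900 = 90%

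The values of r are assumptions.

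**A gap.** The rule gives no verdict when LIPUS beats self-control but not control. On the untreated-area reading at d = 0.5 this happens in about 15% of trials.

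**The case against.** The strongest defence is that the self-control group in the rule means the untreated areas. The Intervention description uses the term for the untreated lung. Trial design {8} and the explanation of comparators {6b} describe the arm as stimulated against non-stimulated areas, and the Discussion repeats, just before the rule, that it is there to remove individual differences. Read so, *fair* means better than control while treated and untreated areas look alike. That is a coherent caution: similarity would then count against a local effect. If the contrast is also the paired one, the rule agrees with the Primary outcome section.

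This defence stands in part. A reader might infer that a truly effective treatment would almost never be called effective. The document does not support that as a general statement: it holds only on the treated-area reading. The target-site definition of AAR and VAR, and the mention of three randomized groups in the same Discussion paragraph, make that reading possible but do not settle it.

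What the defence does not remove is that the words compare one group with another, that the area is not named, and that the untreated-area reading taken literally still compares different patients and discards the pairing. Nor does it touch the last limb.

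A second defence is that this is interpretive prose in a Discussion, that it changes no test or p-value, and that a fuller plan may hold the formal rule. That limits its weight. But the point is not an omission: the text affirmatively states how results become conclusions, and that statement conflicts with another section of the same document.

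**Conclusion.** The concern holds as one of mismatch, ambiguity and mislabelling. The rule adds a LIPUS-arm versus self-control-arm comparison that the Primary outcome section does not plan, leaves the compared area open, and equates non-significance with poor efficacy.

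For a true effect of 1.0 SD, the chance of the verdict *effective* runs from about 2.5% to about 83% by reading alone, against about 80 to 90% for the planned comparisons. At 0.5 SD, about 48 to 61% of trials would be labelled *poor* across the three readings. Failure to beat control alone is about 63% there (100 − 37), but the rule's *poor* also requires no difference from self-control, so 63% is not its rate. Under the paired rule it would be 41% or less.

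These figures assume 22 per arm, equal SDs, the stated effect sizes and no effect of LIPUS on untreated areas. The mismatch and the misreading of non-significance do not depend on them.

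**What to change.** Replace the three-way rule in the Discussion with the comparisons of the Primary outcome section:

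- The efficacy conclusion rests on LIPUS versus control for the primary outcome, reported as a difference with a 95% CI.
- The self-control arm contributes only its paired treated-minus-untreated difference, with a 95% CI, as supporting evidence.
- A non-significant result is reported as inconclusive and interpreted through its CI, not as poor efficacy.

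The cost is a text change. Allocation, data collection and sample size are unaffected. The defect does not require a ban on every LIPUS versus self-control test or a pre-stated smallest worthwhile effect.

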## Strengths and limitations

We proposed and demonstrated a novel approach to promote inflammatory uptake in viral pneumonia. Given that the current clinical recovery mainly depends on the body’s self-limiting and conventional symptomatic treatment, LIPUS, as a new therapy method, might be a major advance in the treatment of viral pneumonia. The clinical application of wearable and easily operative LIPUS without radiation and side effects may be more extensive than limited to viral pneumonia. Combined with the therapeutic mechanism, it is speculated that LIPUS may also play a certain role in the treatment of other types of pneumonia. And it should also have advantages in pediatric patients and home treatment.

This study has two main limitations. First, we only compared the difference between LIPUS treatment and non-treatment and did not compare LIPUS with commonly used clinical anti-inflammatory drugs, immunomodulatory drugs, or anticoagulation, which made the observation of clinical efficacy not comprehensive enough. Second, this is a single-center study. Due to the limited number of wearable US devices, it has not been further developed in other research centers.

To the best of our knowledge, this study is the first clinical study of the efficacy of therapeutic LIPUS in the treatment of viral pneumonia. Compared with drug treatment or other artificial/mechanical assisted treatment equipment, a wearable LIPUS device will be simpler, safer, and more comprehensive and is expected to greatly improve the continuity and compliance of clinical treatment for patients with viral pneumonia.

## Trial status

The first version of the protocol was approved by the institutional ethical committee on June 6, 2022, and this protocol is version 1.0. The design and improvement of the chest wearable LIPUS therapeutic device, as well as the confirmation of ultrasonic stimulation parameters, are currently underway. Patient recruitment and data collection will be carried out in our hospital from October 2022 to October 2023, and data will be collated and analyzed later.

## Data Availability

The datasets generated and analyzed during the current study are not publicly available because the protocol has not been completed at the time of submission but will be available from the corresponding author upon reasonable request.
